#### Neurophysiological Measures

HRV enables this research to look at the activities of PNS, SNS, and their interactions across different experimental conditions (ie, resting baseline, stimulation, recovery conditions). For this study, Polar H2 Heart Rate Monitor (Polar, Finland) is used to measure HRV at 5 kHz sampling rate. There is some evidence that supports the use of Polar heart rate monitors as a valid instrument to measure HRV [79], and ultimately follow the set guidelines for HRV measurement and research [51].

EDA is an autonomic measure of SNS. Because LF bands of HRV have been contested as a true measure of SNS activity, EDA is used as an adjunct measure in this research. The eSense Skin Response-GSR sensor (Mindfield, Germany) measures skin conductance level (SCL) and response (SCR) with a sampling rate of 5 Hz and a resolution of 18 bit, using direct current. The device performs exosomatic measurement with a direct current of 0.50 V through two 5-mm silver-silver chloride (Ag/AgCl) electrode. Although fairly new, the specifications of eSense meet the general publication recommendations for EDA research [52,53].

### Procedures and Paradigm

The experimental protocol used in this part of the study is adapted from SCP, first employed by Miller et al [46], with a few modifications based on a systematic review by Gomez et al [43]. Figure 1 presents the experimental paradigm used in this study. Instead of using various multisensory stimuli, we opt for an auditory stimulus to represent external challenges to the allostatic response. Furthermore, we use 3 conditions, instead of the original resting baseline and stimulation conditions. A 3-min resting baseline period is used to allow sufficient data time points necessary for analysis of autonomic responses (HRV-HF [normalized units (n.u.)] and LF (n.u.); EDA-SCL) [51-53]. During this time, a silent cartoon movie is shown to the child for 200 seconds. At the condition of sensory stimulation, the screen turns blank and the participant receives a block of passive auditory sensory stimulation (a block of 10 trials of a 4 KHz pure tone at 85 dB; each trial lasting for 3 seconds) with a pseudorandomized interstimulus interval of 10 to 15 seconds to avoid adaptation to stimuli. The auditory stimulation condition lasts for approximately 160 seconds. The use of a pure tone is another modification of this research, used from the original fire engine sound, to reduce any emotional responses to familiarity with the stimuli. The loudness is reduced from the original 95 dB to 85 dB to ensure that the intended physiological response is recorded and no other internal events related to louder auditory stimuli [80]. At the recovery condition, the same silent cartoon movie is played for 200 seconds. Previously, the recovery condition was not a part of the original SCP; however, it has been added and adapted in more recent literature. Such recovery conditions may represent physiological regulation related to adaptation, further described in the concept of allostasis. This entire procedure takes around 12 min. The experimental protocol, including the generation of the pure tone for auditory stimuli, is developed and executed using LabView (National Instrument, USA).

**Figure 1 figure1:**
[figure not shown]
Laboratory paradigm.

ANS measures are strongly affected by environmental factors. Thus, in all studies, regardless of the country (Hong Kong or Philippines) where the research is conducted, the same procedures are implemented. Similarly, other factors that influence physiological responses can likewise influence the ANS response. To control for this, parents of the participants are instructed with experiment preparatory reminders: no intake of caffeinated drinks 4 hours before the scheduled testing; no intake of food 1.5 hours before the scheduled testing; no rigorous physical exercise before the scheduled testing; and no treatments/interventions (ie, sensory integration therapy, craniosacral therapy, acupuncture, or any other procedures that could influence ANS activity) 24 hours before the scheduled testing.

During the experimental testing, the body mass index (BMI) is ascertained through measurement of the participants’ height and weight. The Polar H2 chest strap is securely fastened just below the chest muscles. The finger cuffs are fixed around the medial phalanx of the index and middle fingers, opposite the laterality of the participant’s hand. The child sits on a comfortable child-sized chair, facing a 19-inch monitor 3 feet away from him. A set of over-ear open headphones is placed over the child’s ears. During the actual experimental conditions, the room is dimmed to 10 lux (illumination level), temperature set to 23 to 25°C, humidity level at 60 to 80%, and background noise level at 40 to 45 dB. The researcher is located 60 to 80 cm away to the left of the participant, keeping interaction to a minimal. Testing procedures in this research are adapted from a similar previous study by Lai [63] and a systematic review by Gomez et al [43]. These conditions are kept constant across all testings.

### Data Analysis

#### Neurophysiological Data

HRV is acquired using Polar H2 heart rate monitor, recorded in real time, and simultaneously stored using the Polar Trainer 5, directed through infrared signals. The software for HRV analysis used was aHRV (Nevrokard, Slovenia), which uses the current guidelines for HRV analysis [47]. Raw data were converted into aHRV tachogram files. Using the researcher’s observation notes, tachograms are subjected to visual analysis, identifying ectopic beats, movement artifacts, and abnormal noise signals. HRV files are then epoched into specific time events in the experimental paradigm. The epoched tachograms are subjected to correction of artifacts following the guidelines used by Task Force of the European Society of Cardiology [51]. In identifying artifacts for the short-term recordings, aHRV compared values to 20% under or over the mean of the preceding 25 beats [51]. Identified noise artifacts are then edited using proper interpolation, keeping as much of the integrity of the data sample. Data with more than 3% correction from the total normalized HRV data samples were discarded from the analysis. A 512-point Fast Fourier Transform was generated using a Hanning window to minimize spectral leakage at truncated data segments. Frequency domain analysis covered low (LF: 0.04-0.15 Hz) and high (HF:0.15-0.40 Hz) frequency components in its normalized units. The normalized units of LF were used as representatives of sympathetic modulation activity (predominantly), whereas the normalized units of HF were used as representatives of parasympathetic modulation activity using the following formula: LF *or* HF/(total power−VLF)×100, where VLF stands for very low-frequency band.

Ledalab version v.3.2.9, a MATLAB-based computer program, is used to extract EDA using a continuous decomposition analysis (CDA) method [81]. Epoched EDA data are then preprocessed individually using visual analysis and subsequent data grooming to reduce noise, which includes manual smoothing using a 5-second Hann window [82,83] and a filter of a unidirectional first-order Butterworth low-pass filter with a similar cutoff frequency of 5 Hz [83,84]. The traced EDA artifacts are then corrected using a spline interpolation within a 5-second pre/post parameter [85]. The CDA method uses parameters based on the previous works of Benedek and Kaernbach [81], which optimizes the EDA data and applies a 0.2-Hz Gaussian smoothing window within a 10-second grid size to detect significant peaks of >0.05 µS [86]. For the resting baseline and recovery conditions, SCL is extracted by using the *CDA.Tonic* parameter, which computes for the mean tonic EDA within the epoched response window (150-second block), in an aggregated 10-second moving within-window averaging method. In the case of processing the EDA stimulation condition data, a similar CDA method is used (Bateman functions comprising onset, amplitude, 1 and 2 parameters). The software can identify significant peaks of >0.05 µS [87], within a response window of 1 to 4 seconds poststimulus [82,88] across the stimulation condition block that consisted of 10 trials. To represent the sympathetic activity in the form of EDA, *CDA.SCR* was identified [82,87], which was then averaged across trials (0 responses not included) within the stimulation block condition as estimate of mean sympathetic activity, reflecting the individual’s amplitude of responsiveness to sensory stimulus. To remove the impact of within and between-subject variance, analysis was performed using z-transformed individual *CDA.SCR* scores [82]. Furthermore, to correct for skewed distribution of skin conductance data scores and to meet assumptions required for parametric statistical analyses, normalization of SCL and SCR data for each intersection was performed using square root transformation [83,89-91]. This logarithmic transformation is determined as follows: *√(CDA.Tonic)* and *√(CDA.SCR+1)*.

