Sensorial input from the external environment is regulated through neurophysiological mechanisms where reactivity is determined, conventionally, in the form of adaptive responses. The ANS response is conceptualized in this research to include the child’s physiological capacity to receive sensory information, react to such information, and recover thereafter. The capacity to receive sensory information can be represented by the resting baseline (sometimes called as resting, basal, or baseline) condition of the ANS activity and is indexed to establish basal levels to which changes in experimental conditions can be referred to [54-56]. The doctrine of autonomic constraint, as initially proposed by Berntson et al [20], suggests that the ANS activity capacity of magnitude change depends on the set starting point. This starting point, as represented by the resting autonomic functions of PNS and SNS, may be involved in regulation of responses. Exposure to sensory stimuli entails physiological reactions from ANS, which has been previously suggested to be the first system to respond to external challenges. This is characterized by the physiological reactivity during the stimulation condition where patterns of magnitude changes from resting baseline conditions to the point of stimulus presentations are referred to [54-56]. During stimulation conditions, the ANS function levels are measured, but other measures are likewise suggested, such as the mean difference between values at the stimulation and resting baseline conditions [57] or the magnitude of change [58]. The recovery condition is roughly described as the temporal point at which experimental stimulation ceases and conditions similar to the resting baseline conditions are used. To an extent, this condition can indicate adaptability of the child after stimulation. In this research, the concept of allostasis is used to better explain the adaptation that is manifested during the recovery condition. Allostasis allows adapting one’s self to the changes in their environment [59] through autonomic responses that can be facilitated by mediators of allostasis.

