#### Statistical Data

Descriptive statistics involving measures of central tendencies, variation, and dispersion are used to describe the salient characteristics of the data gathered. Demographic data related to participant gender, age, BMI, type of school (ie, public, private), number of parents working, primary caregiver, highest educational attainment of caregiver, family income, and parent’s occupation will be gathered and considered in further statistical analyses. The Shapiro-Wilk test of normal is used to determine normality at baseline of the characteristics of the participants included in the study. Univariate and multivariate tests are likewise used to determine whether there are group and subgroup baseline similarities at critical alpha=.05. Variables deemed as non-normally distributed or significantly different at baseline are used as covariates. General linear modeling is used to determine whether effects of ethnicity or environment (used as the independent variables [IV] in this study) can explain differences in the behavioral measures of the participants at a critical value of alpha=.05. Autonomic regulation is represented in this research as HF (n.u.) and LF (n.u.) of HRV and mean EDA (SCL/SCR) values as multivariates. Multivariate analysis of variance (MANOVA) tests will be used to determine whether effects of ethnicity or environment (used as IV in this study) can explain differences in the multivariate set of DVs, across the different research aims, with the different pairwise combinations in between 3 events (resting baseline, stimulation, and recovery). Effect size is interpreted using the values of Cohen *d*. Statistical analysis will be computed using SPSS version 23.0.

Specific to this report, sample size and power analysis are performed using G*Power version 3.1.9.2 [91,92]. Post hoc analysis of computed achieved power of the pilot data will be ascertained to determine the needed effect size for a subsequent a priori computation of required sample size for MANOVA tests.

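### EDA is a tonic level (SCL) at rest and recovery but a phasic response (SCR) during stimulation, so its change from rest to stimulation cannot be formed

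*Protocol article*

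**What the plan says.** All references are to the Protocol article.

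- **Rest and recovery** (Neurophysiological Data): "For the resting baseline and recovery conditions, SCL is extracted by using the" CDA.Tonic parameter, a mean tonic level over a 150-second block.
- **Stimulation** (same section): the variable is CDA.SCR, the phasic response found "within a response window of 1 to 4 seconds poststimulus" over ten tones, "which was then averaged across trials (0 responses not included) within the stimulation block condition as estimate of mean sympathetic activity".
- **Scaling** (same section): "To remove the impact of within and between-subject variance, analysis was performed using z-transformed individual" CDA.SCR scores. No z-step is stated for SCL. Then "normalization of SCL and SCR data for each intersection was performed using square root transformation", with √(CDA.Tonic) for SCL and √(CDA.SCR+1) for SCR.
- **Analysis** (Statistical Data): autonomic regulation is HF (n.u.), LF (n.u.) and "mean EDA (SCL/SCR) values as multivariates". MANOVA is to be applied with pairwise combinations between the three events.
- **Construct** (Background of the Study): the resting baseline supplies the level against which later change is judged. Reactivity during stimulation is where "patterns of magnitude changes from resting baseline conditions to the point of stimulus presentations are referred to". The same paragraph says that levels during stimulation are measured and that the difference from baseline is a further suggested measure.

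**The concern.** The research question is about regulation of the response to a stimulus. The Introduction ties this to the child's own starting point: rest is the reference, and capacity for change is said to depend on it. For EDA the planned variables give no such reference during stimulation, because the quantity itself changes between conditions.

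The article states both definitions explicitly, so this is not a detail left to an analysis plan. At stake is whether the three-variable outcome can answer a question about change, or only whether groups differ in level at each condition.

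**Working it through.** **Step 1. The EDA variable by condition (Neurophysiological Data)**

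| Condition | Quantity | Window | Scaling |
|---|---|---|---|
| Rest | Tonic SCL | 150-second block | √(CDA.Tonic) |
| Stimulation | Phasic SCR, non-zero trials only | 1 to 4 s after each of 10 tones | z-transformed; √(CDA.SCR+1) |
| Recovery | Tonic SCL | 150-second block | √(CDA.Tonic) |

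No tonic level is defined for stimulation, and no phasic measure for rest or recovery.

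**Step 2. Which changes can be formed**

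| Pair | EDA | HF, LF (n.u.) |
|---|---|---|
| Rest to stimulation | SCL against SCR: no | yes |
| Stimulation to recovery | SCR against SCL: no | yes |
| Rest to recovery | SCL against SCL: yes | yes |

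So two of three EDA pairs are lost. HF and LF are defined in the same way throughout and are unaffected.

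**Step 3. What a subtraction would give (illustration)**

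The documents give no SCR values. Assume amplitudes from 0.05 µS (the plan's peak threshold) to 1.0 µS, and ignore the z-step.

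- √(0.05+1) = 1.02 and √(1.0+1) = 1.41.
- Table 1 gives a pilot resting SCL mean of 1.914 and does not say whether it is already square-rooted.
- If it is: 1.02 − 1.914 = −0.89, up to 1.41 − 1.914 = −0.50.
- If it is raw, √1.914 = 1.383: 1.02 − 1.383 = −0.36, up to 1.41 − 1.383 = +0.03.

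The result reflects the switch of variable and scaling, not a change in sympathetic activity.

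**Step 4. What condition-by-condition tests would show**

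Pilot resting HF is 62.301 (urban) and 52.096 (rural), a difference of 10.205 n.u. Suppose, purely for illustration, that both groups respond to the tones by the same amount Δ.

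- Difference in level during stimulation: (62.301 + Δ) − (52.096 + Δ) = 10.205.
- Difference in change from rest: Δ − Δ = 0.

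A test of stimulation levels sees the full resting gap although the responses are identical. The same holds for LF (29.228 − 24.171 = 5.057), and for SCL between rest and recovery. These pilot differences were not significant (HF *P*=.08, LF *P*=.18), so they serve as an example only. The misreading is not hypothetical, though: the pilot results use resting data alone, and the Discussion still speaks of them as bearing on regulation of response.

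**Step 5. The stated sample size**

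Table 2 is the only size given for the three-variable set, and it reproduces. With f²=0.0625, 4 groups, 3 responses and N=88:

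- λ = 0.0625 × 88 × 3 = 16.5
- df = 3 × 3 = 9 and 3 × (88 − 4 − 3 + 3) = 252
- critical F = 1.9171, power = 0.8094

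This point does not dispute that figure. It is a between-group calculation with no within-child factor.

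**The case against.** The strongest reply is that the plan may never subtract SCR from SCL. In the abstract, pairwise refers to groups, which fits separate group comparisons within each condition. Each of those is valid, and SCR is a proper stimulus-evoked measure. The Introduction also accepts levels during stimulation, so change is not its only metric. All of this stands and it limits the point. It does not remove it, because Statistical Data speaks of combinations between the three events. Read that way, two EDA contrasts are undefined; read the other way, no planned test addresses change.

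A reader might also infer more than the documents support:

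- *That a group with a higher resting level must look different at all three conditions on EDA.* The decomposition separates tonic from phasic activity, and nothing says a higher resting SCL carries into SCR. The argument applies to HF and LF, and to SCL between rest and recovery.
- *That EDA is the only sympathetic measure the plan relies on.* The article calls EDA supplementary and an adjunct. It concedes that LF is contested but still uses it as predominantly sympathetic.
- *That the sympathetic response to the tones goes unmeasured.* SCR measures it. What is missing is tonic change.
- *That the display should be altered, since* "At the condition of sensory stimulation, the screen turns blank" *while a cartoon runs at rest and recovery.* This is a separate design trade-off, the same for every group, and does not by itself create a group difference. The text does not say that the first tone starts as the screen blanks, and the figure is not shown.

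**Conclusion.** The point holds in this limited form. As defined, EDA change cannot be formed for two of the three condition pairs, including rest to stimulation, which the Introduction uses to characterise reactivity. HRV change, SCL change from rest to recovery, and within-condition group comparisons are unaffected. The risk of reporting a resting difference as a difference in regulation depends on the MANOVAs being run condition by condition, which the text allows but does not settle. No stated figure changes. This is a worthwhile, inexpensive improvement and not a fatal defect. The SCR range in the illustration is an assumption, and the conclusion does not rest on it.

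**What to change.** 1. In Neurophysiological Data, extract SCL (CDA.Tonic) from the stimulation epoch too, with the same square-root scaling, and use SCL as the EDA variable in all three conditions. Stimulation lasts about 160 seconds, so the 150-second window used elsewhere fits.
2. Keep SCR as a separate outcome, reported for stimulation only, and remove the combined SCL/SCR entry.
3. In Statistical Data, state that regulation is tested by the group-by-condition interaction (change from the child's own rest) for HF, LF and SCL. Report resting level as its own question.

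The cost is modest: one more parameter exported from a signal the plan already records and decomposes, some extra analysis, and one additional outcome. The results reported so far use resting SCL only, so they are not disturbed. Table 2 does not model an interaction over the three conditions. If only the three rest-to-stimulation changes are tested, its layout of 3 responses and 4 groups carries over, but its effect size would then be an assumption about change, on which the pilot's resting data are silent.

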### Participants

Using a cross-sectional study design, this study compares the autonomic activity in different experimental conditions (resting baseline condition, stimulation condition, and recovery condition) among 4 groups of participants, comprising 2 groups of typically developing children, (1) from different ethnicities (Chinese children in Hong Kong, Filipino children in the Philippines-Urban area); (2) from different geographic environments (Filipino children in Hong Kong, Filipino children in the Philippines-Urban area); (3) from different ethnicity and geographic environments (Chinese children in Hong Kong and Filipino children in the Philippines-Urban area); and (4) from different physical environments (Philippines-Urban area, Philippines-Rural area). Participants will be typically developing boys and girls, aged 7-12 years with no known developmental, neurological, or medical condition. The sample size of n=32 for each group was initially estimated based on the mean change of ANS indices of a previous study with similar but not the same experiment [67] by using the effect size of 0.8 for group differences with the alpha level at .05.

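### The stimulation-phase SCR is z-transformed to remove between-subject variance, yet it is then tested for differences between groups of different children

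*Protocol article*

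**What the plan says.** All the processing steps are in the protocol article, Data Analysis, Neurophysiological Data. For the stimulation block, CDA.SCR is "averaged across trials (0 responses not included) within the stimulation block condition as estimate of mean sympathetic activity", and the result is described as "reflecting the individual’s amplitude of responsiveness to sensory stimulus". The next sentence adds the standardisation: "To remove the impact of within and between-subject variance, analysis was performed using z-transformed individual" CDA.SCR scores. A further sentence, introduced as an additional step, says that "normalization of SCL and SCR data for each intersection was performed using square root transformation". The formulas given are √(CDA.Tonic) for skin conductance level (SCL) and √(CDA.SCR+1) for SCR, and the text calls this square root logarithmic.

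Under Statistical Data, autonomic regulation is represented by HF, LF and "mean EDA (SCL/SCR) values as multivariates". The MANOVA "tests will be used to determine whether effects of ethnicity or environment (used as IV in this study) can explain differences" in that set. SCL is extracted at baseline and recovery, and SCR at stimulation.

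The text does not say whether z is taken within child, within group or over the whole sample. It also does not say whether the root is applied to raw or to standardised SCR.

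**The concern.** Ethnicity and environment are fixed for each child, so any effect they have on SCR lies entirely in the between-child variance. A step meant to remove that variance, if it succeeds, removes the effect the MANOVA looks for. If it does not succeed, it has no role in the plan, and it may pass negative numbers to the square root.

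Stimulation is the only condition in which the tones are delivered, and SCR is its only electrodermal variable. The article includes electrodermal activity because LF is contested as a sympathetic measure (Neurophysiological Measures). If SCR is lost or distorted, the contested LF is the only sympathetic index left in the condition that the research question is about.

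**Working it through.** **Figures in the plan.** The article gives no figure for the SCR score. Its sample size can be checked. With f² = 0.0625, 4 groups, 3 response variables and N = 88 (Table 2), s = min(3, 3) = 3. Then V = 3 × 0.0625/1.0625 = 0.1765, λ = 3 × 0.0625 × 88 = 16.5, df are 9 and 252, critical F is 1.9171 and power is 0.8094, as printed. No SCR datum enters this, and the pilot analysis used resting SCL. Neither depends on the z-step.

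**Notation.** x_ij is the SCR of child i on tone j (10 tones), and m_i is the mean over that child's non-zero responses.

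**1. z within child, same trials standardised and averaged.** z_ij = (x_ij − m_i)/s_i. These sum to 0 for each child, so every child's mean is 0 and √(0+1) = 1 for everyone. In simulation the largest group difference was 2 × 10⁻¹⁶, which is rounding error.

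**2. z within child over all 10 tones, zeros then left out of the average.** With k non-zero responses the child's overall mean is (k/10)m_i, so the score is m_i(1 − k/10)/s_i. It is not constant. But m_i and s_i scale together, so doubling all of a child's responses leaves the score unchanged. Amplitude is still lost.

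**3. z within group.** Each group mean is set to 0, so the difference in means is 0.

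**4. z over the whole sample.** z_i = (m_i − m̄)/s, with the same m̄ and s for every child. This is a linear rescaling, so the MANOVA statistic is unchanged and between-subject variance is not removed. If √(z_i+1) follows, it has no real value when m_i < m̄ − s.
- Normal: Φ(−1) = 15.9%, or 0.159 × 128 ≈ 20 children.
- Lognormal with median 1 and log-SD σ: mean = exp(σ²/2), CV = √(exp(σ²) − 1), share = Φ(ln[mean × (1 − CV)]/σ). For σ = 0.2: mean 1.0202, CV 0.2020, 1.0202 × 0.7980 = 0.8141, ln = −0.2057, Φ(−1.028) = 15.2%.
- Likewise 12.6% at σ = 0.4, 6.8% at 0.6 and 0.05% at 0.8. At 1.0 the CV is 1.31, so the SD exceeds the mean and the share is 0.

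**5. Root of raw SCR, then whole-sample z.** SCR is non-negative, so the root always exists, and the z-step is again a linear rescaling.

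**Simulation of the consequence.** Assumptions: two groups of 32, 10 tones, lognormal amplitudes with median 0.3 µS, trial log-SD 0.5, 20% zero responses in both groups (at least two non-zero per child), a true shift of 0.8 between-child log-SD, univariate t test at 0.05, 1000 runs. Rejection rates:

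| Between-child log-SD | Raw mean (same with whole-sample z) | Root of raw mean + 1 | Reading 2 | Reading 3 | Reading 4 with root, undefined children dropped |
|---|---|---|---|---|---|
| 0.2 | 62.6% | 63.0% | 4.4% | 0% | 39.0% |
| 0.4 | 78.9% | 79.9% | 6.2% | 0% | 61.6% |
| 0.6 | 78.6% | 81.6% | 5.6% | 0% | 75.3% |
| 0.8 | 74.8% | 80.8% | 5.0% | 0% | 81.4% |
| 1.0 | 68.2% | 77.5% | 5.4% | 0% | 79.5% |

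The Monte Carlo standard error near 5% is √(0.05 × 0.95/1000) = 0.7 points, so the reading 2 column is consistent with alpha. In reading 4 the children lost are the weakest responders, so the loss is informative. At log-SD 0.8 and 1.0 hardly any are lost, and there is no power penalty.

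**The case against.** A reader might infer that the stimulation SCR is bound to end up either constant or undefined. The article does not support that.

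- The root is printed on CDA.SCR, parallel to √(CDA.Tonic), which is not standardised. The linking word adds a step without clearly fixing the order. Raw SCR may be meant, in which case a root followed by a whole-sample z is defined and harmless.
- Averaging over trials is described before the z-step. Taken in that order there is one value per child, which cannot be standardised within child. This weakens reading 1.
- Even within child, the score is not constant if z is taken over all 10 tones and zeros are then left out.
- The SCR distribution is not given, so the share of undefined children is an assumption, and it can be nil.

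All four points stand. They show that the outcome depends on unstated choices. They do not rescue the stated purpose, because the harmless reading is precisely one that leaves between-subject variance in place.

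A reader might also conclude that the square root should give way to a log. That depends on an assumed SCR scale and is a matter of choice, so it is not part of this point.

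On scope, the objection is right that one of three dependent variables, in one of three conditions of an exploratory study, is affected.

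**Conclusion.** The conflict between purpose and test is in the article's own text and does not depend on any simulation. A z-step that does what the article says it is for, within child or within group, removes the group difference in SCR amplitude. A whole-sample z leaves the test unchanged and does not do what it is said to do. If the root is then taken of z, children below −1 SD drop out: 15.9% under normality, 15.2% to 6.8% for lognormal log-SD 0.2 to 0.6, about 0 from 0.8. One combination, a root of raw SCR with a whole-sample z, does no harm, and there the z-step is superfluous.

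The percentages and power figures rest on assumed SCR distributions. The alpha-level rejection under reading 2 also assumes equal zero-response rates in the groups; if these differed, the score could differ, but through response frequency rather than amplitude. The effect is confined to stimulation-phase SCR. It should be settled before the group comparisons are run.

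**What to change.** In Neurophysiological Data, delete the z-transformation for the between-group test. State that the square-root transform is applied directly to each child's raw, non-negative mean SCR, in the same way in all groups. Keep the present rule on zero responses; if it is to change, say so explicitly, since averaging over all 10 tones with zeros counted would be a different outcome. Replace the word logarithmic with square-root.

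If a z-score is wanted for display, state that it is taken over the whole sample and after the root.

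The cost is one or two sentences. Stored recordings can be re-scored, and neither data collection nor the sample size changes.
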